## **8.2. Study setting**

This is a single-site study (Northumbria University). This study will be delivered using the internet and there are no geographic restrictions.

## **8.3. Eligibility criteria**

Participants will be provided with an online information sheet (Appendix 1) and will be required to provide informed consent, which will be recorded electronically (Appendix 2), before any study procedures can be completed.

### *8.3.1. Inclusion criteria*

Both healthy good sleepers, who do not report having any sleep problems, and individuals who do report current sleep problems (between two weeks and three months), will be recruited for the present study.

To participate, the following inclusion criteria will apply (to good and poor sleepers):

- 1) individuals must be aged 18 years or above
- 2) individuals must consider themselves to have a sufficient level of English comprehension to be able to understand and complete all study measures.

Self-reported poor sleepers will need to meet criteria for acute insomnia, as based on the definition included in the Diagnostic and Statistical Manual of Mental Disorders (DSM-5; American Psychiatric Association, 2013)

Specifically, individuals with poor sleep must report:

- 1) difficulties in falling asleep, staying asleep, or awakening too early for at least three nights per week, for a time period of between two weeks and three months
- AND**
- 2) distress or impairment caused by sleep loss.

Both 1 and 2 must occur despite the individual having an adequate opportunity for sleep.

### *8.3.2. Exclusion criteria*

Individuals who report having chronic sleep problems (i.e. where they have existed for more than three months immediately prior to providing consent) will not be eligible to participate nor will those who are actively seeking treatment for their sleep problems, irrespective of how long they have had the sleep problem. Additionally, participants who have a self-reported history of head injury, or who have had a diagnosis of schizophrenia, epilepsy or personality disorder cannot take part as the distraction techniques involved in the intervention may increase rumination and this may influence the effectiveness of the intervention.

## **8.4. Intervention**

Participants who receive the intervention will be provided with an online version of a self-help leaflet (Appendix 3). A printed version of this leaflet has been successfully used in previous treatment studies, which have been conducted by our research group (Boullin et al., 2016;

Ellis et al., 2015; Randall et al., 2019). Participants will be encouraged to download, save or print out this leaflet, which will be provided in PDF format. There will be no restrictions on use and participants will be encouraged to refer to this as often as they wish to.

Briefly, this self-help leaflet aims to improve sleep by identifying and addressing sleep-related dysfunctional thinking by providing education about sleep, providing techniques to distract from intrusive worrisome thoughts at night, and providing guidelines for sleep-related stimulus control.

Treatment adherence will be formally monitored. This will be done by verifying that participants have downloaded, or have viewed, the information leaflet from the Qualtrics system. There are restrictions on pharmacological or non-pharmacological concomitant care before and during study participation as outlined in Section 8.3. This is necessary in order to be able to verify whether the intervention can reduce symptoms of acute insomnia.

## **8.5. Outcomes**

### *8.5.1. Primary Outcome Measures*

The primary outcome measures will be insomnia severity, as measured using the Insomnia Severity Index (Bastien, Vallières, & Morin, 2001), assessed prior to the intervention and one week, one month and three months post-intervention, relative to baseline.

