| Target sample size                            | 60 (30 poor sleepers, 30 good sleepers)                                                                                                                                                                                                                                                                                                                                                                                                                                                                                                                                                                                                                                      |
| Recruitment status                            | Not yet recruiting                                                                                                                                                                                                                                                                                                                                                                                                                                                                                                                                                                                                                                                           |
| Primary outcome(s)                            | Insomnia Severity Index scores (post-intervention)                                                                                                                                                                                                                                                                                                                                                                                                                                                                                                                                                                                                                           |

|                                                            |                                                                                                                                                                                                                           |

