|------------------------------------------------------------|---------------------------------------------------------------------------------------------------------------------------------------------------------------------------------------------------------------------------|
| Key secondary outcomes                              | 
 
• Subjective mood scores (PHQ-9 and GAD-7)
 
• Measures of sleep continuity derived from sleep diaries
 
• Insomnia Severity Index pre-post change scores
 
 |
| Study start date (date of initial ethical approval) | 8 April 2020                                                                                                                                                                                                              |
| Study end date                                      | 8 April 2022                                                                                                                                                                                                              |
| Study duration                                      | 24 months                                                                                                                                                                                                                 |

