### **7.2. Study objectives**

#### *7.2.1. Primary objective*

The primary aim of the present study is to examine the efficacy of an online intervention for poor sleep in the context of an ongoing stressful major life event, by assessing if this intervention can reduce insomnia severity at short-term (one week post-intervention) and long-term (one and three months post-intervention) follow-up.

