### **8.9. Procedure**

The entire study will be conducted online, and will be delivered using Qualtrics. The full list of assessments to be completed at each time point is included in Table 1.

The end of study will be defined as the final follow-up time point (i.e. 3 months follow-up), or the final study measure completed, should the participant drop out of the study before this point.

Table 1: list of study assessments to be completed at each time point

| Measure                                               | Baseline | Pre-intervention | Post-intervention | One week follow-up | 1 Month follow-up | 3 Month follow-up |
|-------------------------------------------------------|----------|------------------|-------------------|--------------------|-------------------|-------------------|
| Demographic and physical/psychiatric health questions | X        |                  |                   |                    |                   |                   |
| SDS-CL-25                                             | X        |                  |                   |                    |                   |                   |
| KSS                                                   | X        | X                | X                 | X                  | X                 | X                 |
| MADRE                                                 | X        |                  |                   |                    | X                 | X                 |
| GAD-7                                                 | X        | X                |                   | X                  | X                 | X                 |
| PHQ-9                                                 | X        | X                |                   | X                  | X                 | X                 |
| PSS                                                   | X        | X                |                   | X                  | X                 | X                 |
| SF-36                                                 | X        |                  |                   |                    | X                 | X                 |
| Impact of Event Scale-R                               | X        |                  |                   |                    |                   |                   |
| Perceived Vulnerability to Disease                    | X        |                  |                   |                    |                   |                   |

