#### *8.9.4. Post-intervention*

Following the intervention, all participants will complete daily CSD-M, KSS and STAI measures for one week. Good sleepers who do not receive the intervention will also complete daily CSD-M, KSS and STAI measures.

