#### *8.9.5. Follow-up periods*

At one week follow-up (i.e. one week after the intervention), or an equivalent time point for good sleeper participants who do not receive the intervention, participants will complete the KSS, GAD-7, PHQ-9 and ISI. At one month and three months follow-up, participants will complete the KSS, GAD-7, PHQ-9, SF-36, MADRE and ISI. Participants will receive a debrief (Appendix 4) at the end of the study.

Assessments will be modified at follow-up points to only ask about the previous week, with the exception of the SF-36, which will not be modified.

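### The primary ISI outcome is defined inconsistently, and the contrast, time point and scale to be reported as the treatment effect are left open

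*Combined protocol and SAP*

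**What the plan says.** All references are to the combined protocol and SAP.

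- **Section 1, primary outcome:** "Insomnia Severity Index scores (post-intervention". The entry ends there, with no week or month attached.
- **Section 1, key secondary outcomes:** these include "Insomnia Severity Index pre-post change scores".
- **Section 7.2.1:** the aim is to "reduce insomnia severity at short-term (one week post-intervention) and long-term (one and three months post-intervention) follow-up". That gives three times, unranked.
- **Section 8.5.1:** the primary outcome measures (plural) are the ISI "assessed prior to the intervention and one week, one month and three months post-intervention, relative to baseline".
- **Table 1 (Section 8.9):** the later columns run "Post-intervention | One week follow-up | 1 Month follow-up | 3 Month follow-up". The ISI row is marked at baseline, pre-intervention and the three follow-ups. It is blank under the first of the columns just quoted.
- **Section 8.9.4:** "Following the intervention, all participants will complete daily CSD-M, KSS and STAI measures for one week". The ISI is not among them. It returns in Section 8.9.5 at one week, when "participants will complete the KSS, GAD-7, PHQ-9 and ISI", and again at one and three months.
- **Sections 8.6 and 10:** one 4 (group) x 5 (time) mixed ANOVA on the ISI, powered for the interaction. Section 10 follows a significant interaction with post hoc tests, without naming a contrast or a time point. The only multiplicity adjustment it names is for sleep continuity, a secondary outcome.

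**The concern.** Change from baseline is primary in Section 8.5.1 and secondary in Section 1. One undated time in Section 1 stands against four assessments in Section 8.5.1 and three in Section 7.2.1. One of the four precedes the leaflet, so it cannot measure the leaflet's effect.

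The term *post-intervention* also has two meanings. In Table 1 and Section 8.9.4 it is the diary week, when no ISI is taken. In Sections 7.2.1, 8.5.1 and 10 it describes the one-week, one-month and three-month follow-ups.

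The trial's claim will be a statement about the leaflet against wait-list in poor sleepers. The omnibus test does not make that statement; a post hoc comparison will. If the time point and the scale (score or change) of that comparison are not fixed, a favourable one among several can be presented as the primary result, and different sections would support different claims.

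**Working it through.** **1. Reproduce the planned sample size.** Inputs from Section 8.6: 4 groups, 5 times, 95% power, medium effect 0.25, 20% drop-out. Not stated, so assumed: alpha 0.05, correlation 0.5, sphericity. For the interaction, λ = f² × N × 5 / (1 − ρ), with df 12 and 4(N − 4).

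- N = 48: λ = 0.0625 × 48 × 5 / 0.5 = 30.0; df 12 and 176; power 0.968.
- N = 44: λ = 27.5; df 12 and 160; power 0.949, just short.
- Drop-out: 48 / 0.8 = 60, or 15 per group and 12 after drop-out.

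The plan's 48 and 60 reproduce with Cohen's f = 0.25. The printed symbol is f²; taken literally it would give N = 16. The 95% belongs to the omnibus interaction and to no single contrast.

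**2. What the omnibus test fixes.** Subtracting each participant's baseline from all five of that participant's values removes one constant per person. The group-by-time interaction ignores such constants, so its F test is identical for scores and for change. The scale is therefore open only in the post hoc step.

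**3. What the open post hoc step can cost.** Simulation: 20,000 trials per setting, four groups of 12, five equally correlated normal measurements (ρ 0.5 and 0.7, assumed), no leaflet effect. The improvement shown is added equally to both poor-sleeper arms at the three follow-ups; good sleepers do not change. A trial counts if the interaction has p < 0.05 and at least one unadjusted intervention versus wait-list t-test has p < 0.05.

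| Assumed improvement in both poor-sleeper arms | Interaction significant | Plus any of 3 scores | Plus any of 3 scores or 3 changes from baseline |
|---|---|---|---|
| None | 5% | about 1% | about 2.5% |
| 0.5 SD | 34-57% | 6-7% | 11-15% |
| 1 SD | 96-100% | 11-12% | 21-22% |

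Without the interaction as a gate, the two right-hand columns would be about 11-13% and 21-22% in every row. The gate protects when nothing changes. It stops protecting when poor sleepers recover and good sleepers stay level, because that difference alone makes the interaction significant.

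**4. Power of the contrast of interest.** Two-sided 0.05, normal approximation, d = 0.8 assumed.

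- 12 per arm: 0.8 × √(12/2) = 1.96; power = Φ(1.96 − 1.96) = 50%.
- 15 per arm: 0.8 × √(15/2) = 2.19; power = Φ(2.19 − 1.96) = 59%.
- At 12 per arm, d = 0.5 gives 23% and d = 1.0 gives 69%.

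**5. Are concurrent ISIs available?** Section 8.9.3 gives the immediate arm the leaflet after the one-week baseline, around Day 8. Its one-month visit is then about Day 8 + 28 = 36 to Day 8 + 30 = 38, if days count from enrolment. The wait-list arm has an extra ISI on Day 28 and another just before its own leaflet. If its 28-day delay starts at Day 8, that last ISI falls near Day 36; if it starts at enrolment, near Day 28. Figure 2, which would settle the numbering, is not reproduced in the text available here.

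**The case against.** Four points can be made for the plan.

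- **The ISI is collected.** A reader might infer from Table 1 that the Section 1 primary outcome falls at a time with no ISI. The documents do not establish that. Sections 7.2.1, 8.5.1 and 10 attach *post-intervention* to follow-ups where the ISI is taken, so Section 1 may be shorthand for them. This stands: the label is ambiguous, and the outcome is not shown to be uncollected. The shorthand would still cover three visits and select none, and the conflict between score and change remains.
- **The primary analysis is specified.** Sections 8.6 and 10 give the same omnibus test, with post hoc tests only after a significant interaction. This stands as well. It rules out quoting the ungated 11-13% and 21-22% as the error rate of the plan under no effect.
- **The gate may be enough.** It is enough if no group changes. The leaflet in Appendix 3 itself tells readers that short-term insomnia usually resolves as stress eases, so improvement in both poor-sleeper arms is plausible. The documents give no figure for its size.
- **The analyst is blinded until the study ends (Section 8.11), and there is no interim analysis (Section 10).** This lowers the risk of selection. It does not say which result is primary.

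**Conclusion.** Wrong as written. Sections 1 and 8.5.1 conflict on whether the primary variable is a score or a change, and no section names one primary time point or one treatment contrast. That conclusion rests on the text alone.

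The size is conditional. With 12 per arm, no leaflet effect and correlation 0.5 to 0.7, the chance of a significant interaction plus a nominally positive intervention versus wait-list result is about 1% (scores) or 2.5% (scores or change) if nothing changes. It is about 11-12% or 21-22% if both poor-sleeper arms improve equally by about 1 SD. Correlation, improvement and equal variances are assumptions.

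A reader might also infer that the Day 28 wait-list ISI already supplies a clean one-month comparison. The text does not show this: the immediate arm's one-month visit may fall about a week later.

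**What to change.** Before enrolment (Section 1 gives the status as not yet recruiting):

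1. State one identical primary endpoint in Sections 1, 7.2.1, 8.5.1 and 10: ISI in poor sleepers, immediate versus wait-list, at one named time point when the wait-list arm is still untreated, adjusted for baseline ISI.
2. Before naming that time, check against Figure 2 which existing ISI assessments in the two arms are concurrent. The Day 28 wait-list ISI is a candidate. If no pair matches, an added or moved assessment would be needed.
3. Make the other follow-ups and all change scores secondary. Keep the pre-intervention ISI as a measurement if wanted, but do not list it as an outcome, and say whether it stays as a level of the ANOVA.
4. Use *post-intervention* in one sense throughout, and check that the registry entry matches.
5. State in Section 8.6 that the 95% power applies to the omnibus interaction, and give the power of the chosen contrast at 15 per arm and at 12 after drop-out.

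The cost is mainly wording and a registry check. The real downside is that fewer results can be called primary and the stated power becomes less favourable. The sponsor would then have to decide whether the sample size is adequate for that contrast.

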### *8.5.2. Secondary Outcome Measures*

The following measures are considered to be secondary outcome measures:

- 1) Subjective mood (subjective depression and anxiety), measured using the 7-item Generalised Anxiety Disorder Questionnaire (GAD-7) and 9-item Patient Health Questionnaire (PHQ-9). These will be assessed immediately prior to the intervention, one week, one month and three months post-intervention and will be compared to baseline.
- 2) Subjective sleep continuity (referring to the number of awakenings (NWAK), wake after sleep onset (WASO), total sleep time (TST), sleep onset latency (SOL) and sleep efficiency (SE%)), as derived from subjective sleep diaries (Carney et al., 2012), before and after the intervention.

## **8.6. Sample size**

The sample size was calculated on the basis of the primary hypothesis.

An *a priori* power analysis, conducted using G\*Power 3.1 (Faul, Erdfelder, Buchner, & Lang, 2009), indicated that a minimum of 48 participants are required on the basis of an expected medium effect size ( $f^2 = 0.25$ ) at 95% power for the primary outcome measure (ISI). This was calculated using a 4 (group: poor sleeper / wait-list control / good sleeper intervention / good sleeper no intervention) x 5 (time point: baseline / pre-intervention / one week post-intervention / one month post-intervention / three months post-intervention) mixed analysis of variance (ANOVA) with an expected interaction.

It is anticipated that there will be an overall drop-out rate of 20% ( $n = 12$ ) during the study and therefore a total sample size of 60 is required. An equal number of participants will be recruited to each group ( $n = 15$ ). Poor and good sleepers will be recruited at a 1:1 ratio (30:30 participants).

### **8.7. Recruitment Strategy**

The URL to the study will be placed online and this will be publicised to potential participants using the Northumbria University website and social media channels (e.g. the Northumbria University Twitter and Facebook account). The URL will also be made available to participants through the ISRCTN trial registration page.

There will not be any financial incentive for participation and the treatment will be offered free of charge to participants. As this is an intervention study, which is delivered online, we do not anticipate that there will be any difficulties with recruitment during the study period.

### **8.8. Measures**

#### *8.8.1. Demographic and physical/psychiatric health information*

Participants will also be asked to provide a brief medical (physical and psychiatric) history and list of current medication, as well as occupational information (e.g. job title and role). Participants will also be asked questions which are related to COVID-19, including whether they have had a test for, a diagnosis of, or have shown symptoms of COVID-19, as well as whether or not they were furloughed (i.e. that they were placed on a temporary leave of absence from work by their employer), or were made unemployed during this period.

This information is required should a sufficient number of individuals participate; this will enable us to examine whether these variables impact on poor sleep, or the effectiveness of the intervention. For example, we will be able to assess whether individuals who are in particular job roles (e.g. healthcare) or with a significant number of existing health conditions, have poorer sleep quality in the context of the pandemic. To provide an indication of general health status, participants will complete the 36-Item Short Form Survey Instrument (SF-36; Ware & Sherbourne, 1992).

